#### Interim analyses {21b}

There will be a safety stop after enrolment of 50 patients in the USA per the FDA. The 90-day safety data of the first 30 patients will be provided to the FDA to request approval to complete enrolment.

#### Methods for additional analyses (e.g., subgroup analyses) {20b}

As a supplementary analysis, the primary endpoint will be evaluated in a per protocol analysis (excluding subjects with protocol deviations) and ITT analysis. No supplementary of sensitivity analyses are planned for the safety and secondary endpoints.

#### Methods in analysis to handle protocol non-adherence and any statistical methods to handle missing data {20c}

By definition, the primary analysis of primary endpoint will be based on available data only, and no imputation for missing data will be performed. The supplementary analysis of primary endpoint based on the ITT analysis set will likely include some subjects who are excluded from the mITT analysis set and do not have evaluable data for the primary endpoint. Subjects who die prior to reaching the 90-day primary endpoint without experiencing any of the primary endpoint outcomes will be excluded from analysis. Data for any other subjects that do not have evaluable data at day 90 will be imputed using multiple imputation in the ITT analysis. The analysis of secondary endpoints will be based on available data only, with no imputation for missing data. Subjects who die or withdraw from the study for other reasons prior to experiencing a specific adverse event will be included in the denominator and assumed to have not experienced the event.

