#### Outcomes {12}

##### Primary endpoint

The primary endpoint is a composite endpoint defined as the occurrence of any of the following within 90 days of surgery:

Wound infection defined in accordance with the Centers for Disease Control and Prevention guidelines as deep incisional (cat II) or organ or space infection (cat III) [8].Intraoperative CSF leakage after device application at a positive end expiratory pressure (PEEP) of 20 cm H_2_O.Percutaneous CSF leakage confirmed by β-2 transferrin test.Pseudomeningocele requiring puncture, external lumbar drainage or surgical re-intervention.Pseudomeningocele >20 cc as confirmed on MRI.

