##### Secondary endpoints

*Safety*
Device-related adverse events (AEs) and serious adverse events (SAEs) throughout the study up to 90 days after surgery.Complications requiring surgical re-intervention up to 90 days after surgery.

*Performance*
Any pseudomeningocele as confirmed on magnetic resonance imaging (MRI) at day 90.Volume of pseudomeningocele as determined on MRI at day 90.Ease of use and application of the LIQOSEAL

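### Counting withdrawn patients as free of adverse events understates 90-day risk, and the day-90 MRI endpoints miss pseudomeningoceles treated and resolved earlier

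*Protocol article*

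**What the plan says.** Section {20c} of the protocol article first gives a general rule: "The analysis of secondary endpoints will be based on available data only, with no imputation for missing data". It then gives a rule for adverse events. Patients who die or withdraw before a specific adverse event "will be included in the denominator and assumed to have not experienced the event".

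Section {20b} adds: "No supplementary of sensitivity analyses are planned for the safety and secondary endpoints". Section {20a} places the safety analyses on the ITT set. Section {18b} keeps data collected up to withdrawal and compares reasons for withdrawal between arms as a check for bias.

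The secondary safety endpoints include "Device-related adverse events (AEs) and serious adverse events (SAEs) throughout the study up to 90 days after surgery", and complications that need surgical re-intervention over the same period. The two MRI performance endpoints are "Any pseudomeningocele as confirmed on magnetic resonance imaging (MRI) at day 90" and "Volume of pseudomeningocele as determined on MRI at day 90". The primary composite has a separate component for treated cases: "Pseudomeningocele requiring puncture, external lumbar drainage or surgical re-intervention".

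**The concern.** There are two separate weaknesses.

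**Withdrawals in the adverse-event proportions.** A patient who withdraws on day 20 has unknown status from day 20 to day 90. Keeping that patient in the denominator with no event fills the gap with the most favourable value. This sits awkwardly beside the preceding sentence, which says that nothing is imputed. It also differs from the ITT analysis of the primary endpoint in the same section, where non-evaluable patients other than deaths are multiply imputed. Safety is part of the objective in section {7}, and the rule pulls risks down and shrinks true differences between arms. In a trial that asks whether the new device is no worse, that is the unsafe direction. Nothing planned would show how much the assumption matters.

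**Treated pseudomeningoceles in the MRI endpoints.** Day 90 is the only postoperative MRI that the article schedules (sections {13} and {18a}). A pseudomeningocele that was punctured, drained or repaired and has gone by then gives a clear scan. Read as written, the patient has no pseudomeningocele and a volume of zero, yet is a primary-endpoint failure. An arm with more successfully treated collections could look better on both MRI endpoints.

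**Working it through.** **The plan's own figure.** The article gives no figure for the secondary endpoints. Its sample size reproduces: with 91% success in both arms, a 10% margin, one-sided 5% and 80% power, n = (1.645 + 0.842)² × 2 × 0.91 × 0.09 / 0.10² = 101.3, so 102 per arm. Dividing by 0.90 for attrition gives 113.3, so 114 per arm and 228 in total. None of what follows changes this.

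**Inputs.** Attrition d = 10% is from section {14}. The only event rate in the article is 9% (100% less 91% success), which belongs to the primary composite; I borrow it as an illustrative adverse-event risk. The 20% risk, the 15% versus 5% attrition split and the shares below are assumptions.

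**Effect on one arm.** Let p be the true 90-day risk and d the share who withdraw.
- Withdrawn patients contribute no follow-up: reported risk = p(1 − d).
- They contribute half the follow-up on average, with events spread evenly over 90 days: reported risk = p(1 − d/2).

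| True risk (assumed) | d | No follow-up | Half follow-up |
|---|---|---|---|
| 9% | 10% | 8.1% | 8.55% |
| 20% | 10% | 18% | 19% |

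The relative understatement is d/2 to d, so 5 to 10%.

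**Effect on the comparison.**
- Equal attrition and equal risk: no false difference.
- Equal 10% attrition, true risks 20% and 10%: with no follow-up, 18% and 9%, so a 10-point difference shrinks to 9.
- Attrition 15% versus 5%, equal true risk of 9%: 7.65% versus 8.55% (0.9 points) with no follow-up; 8.325% versus 8.775% (0.45 points) with half.
- The same split at 20%: 17% versus 19% (2 points), or 18.5% versus 19.5% (1 point). The arm with more dropout looks better.

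**Informative dropout.** Take d = 10%, no follow-up, and a risk among withdrawals of k times the completers' risk. Reported/true = 0.9/(0.9 + 0.1k). For k = 2 this is 0.818, an understatement of 18%; for k = 3 it is 0.75, or 25%.

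**MRI endpoint.** If a share P ever has a pseudomeningocele and a fraction f of these is treated and resolved by day 90, the scan shows P(1 − f).

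| P (assumed) | f = 10% | f = 25% | f = 50% |
|---|---|---|---|
| 10% | 9% | 7.5% | 5% |
| 20% | 18% | 15% | 10% |

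**The case against.** **The rule could be read as applying to every secondary endpoint.** It does not. It is worded for adverse events. A patient with no day-90 scan is left out of the MRI endpoints under the available-data rule and is not scored as event-free.

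**Deaths could be thought to be miscounted.** They are not. A patient who died without a given event did not have that event. An estimator with death as a competing event leaves that patient event-free too.

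**The two sentences in {20c} could be called a contradiction.** They can also be read as a general rule followed by a specific denominator rule, and a crude proportion over the safety set is a conventional summary. The wording needs reconciling; it does not prove an error on its own.

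**Leaks could be thought to be hidden.** They are not lost overall. A treated pseudomeningocele fails the primary composite, and a surgical repair also counts under the re-intervention endpoint. A day-90 MRI endpoint is legitimately a measure of status at day 90. Even so, the article does not say how to read a clear scan after treatment, and a volume of zero for such a patient misleads.

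**Section {18b} already offers protection.** Data up to withdrawal are kept, so only later events are lost, and reasons for withdrawal are compared. That limits the loss but does not recover those events, and no analysis is tied to the comparison.

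**The effect is small.** At 9% risk and 10% attrition the shift is under one point. This stands, and it limits the weight of the point.

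**Conclusion.** The concern holds in a limited form. The withdrawal rule understates 90-day adverse-event risk by about 5 to 10% in relative terms at 10% attrition. This assumes that all attrition is withdrawal, that withdrawal is unrelated to risk, and that withdrawn patients contribute between none and half of the follow-up. If most events come soon after surgery and most withdrawals come later, the loss is smaller. If withdrawn patients have two to three times the risk and contribute no follow-up, it is 18 to 25%.

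A reader might infer that the rule generally favours one arm. The documents do not support that: a false difference needs unequal or informative attrition, and the article predicts neither. Both are possible, since section {18b} lists adverse events as a reason for leaving and section {18a} says that postoperative assessments are not blinded.

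The MRI weakness follows from the endpoint definitions, not from the missing-data rule. Its size depends on how many collections are treated and resolved before day 90, for which the article gives no figure. The primary composite and the sample size stand. This should be corrected, but it does not threaten the main conclusion.

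**What to change.** 1. Reconcile the two sentences in {20c}: say that the no-event rule defines crude adverse-event proportions only.
2. Beside those proportions, report the 90-day cumulative incidence of adverse events and surgical re-interventions by arm (Aalen-Johansen, withdrawal censored, death as a competing event).
3. Add a simple sensitivity analysis for withdrawals, for example with a raised risk after withdrawal, because censoring assumes uninformative dropout. Amend {20b} to allow it.
4. Count a pseudomeningocele that met the treatment component of the primary endpoint before day 90 as an event in the MRI presence endpoint. Do not count collections merely seen clinically, since those assessments are unblinded.
5. Do not enter the volume of these treated cases as zero; for example, give them the worst rank in a rank comparison.

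The cost is slightly more analysis work, with no new patients or visits. The treated cases are already needed for the primary endpoint. Cumulative incidence also needs event and withdrawal dates; the article requires the reason for discontinuation but does not mention its date, so confirm that it is recorded. The downside is that the MRI presence endpoint is no longer a pure day-90 status measure; the plain scan result can be shown beside it.

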#### Plans to give access to the full protocol, participant-level data, and statistical code {31c}

The full protocol will not be published. An abbreviated protocol has been registered at ClinicalTrials.gov (number NCT04086550) prior to study initiation. The participant-level dataset and statistical code will not be granted for public access.

### Oversight and monitoring

#### Composition of the coordinating center and trial steering committee {5d}

There are two coordinating investigators for this trial: one from the USA and one from Europe. The study will be managed by a project manager and study coordinator employed by the sponsor. The sponsor’ study team, a PhD student, and both coordinating investigators will meet at a weekly basis. Day-to-day performance of the trial at the sites will be performed by site personnel trained for the study. Contact with the sites between sponsor, coordinating investigators, and sites’ study personnel will be at a regular basis, dependent on the need for the site based upon enrolment rate and site proficiency. The day-to-day performance of the trial by the sites will be supported and monitored by an independent CRO, who will be in contact with the sponsor, coordinating investigators, and sites’ study staff at a regular basis based on the need for the site based upon enrolment rate and site proficiency. An independent data monitoring committee (DMC) will be appointed consisting of at least 3 specialists in the field of neurosurgery, who will assess patients’ safety and trial progress based upon enrolment rate and (serious) adverse events on a regular basis.

#### Composition of the data monitoring committee, its role, and reporting structure {21a}

The data monitoring committee (DMC), consisting of at least 3 specialists in the field of neurosurgery, will review data relating to safety and performance and to ensure the continued scientific validity and merit of the study. Further details regarding the DMC can be found in its charter (Supplementary Material 2). Following each meeting, a formal report will be prepared, which will be sent to the sponsor after approval of all members of the DMC. The DMC is independent from the sponsor, and members have no competing interests.

#### Adverse event reporting and harms {22}

During the study, (serious) adverse events and (serious) anticipated and unexpected adverse device effects will be recorded; reporting will be done from point of enrolment till end of study.

The (principal) investigators shall report all adverse events and device deficiencies in the appropriate sections of the e-CRF and provide where requested by the sponsor, the necessary clinical or technical information that may contribute to clarifying the circumstances.

The (principal) investigators shall report all serious adverse events (SAEs) and device deficiencies (DDs) that might have led to a SAE if (a) suitable action had not been taken or (b) intervention had not been made or (c) if circumstances had been less fortunate, and new findings/updates in relation to already reported events to the sponsor and record in the e-CRF within 24 h after awareness of the event.

Any other reportable events as described above or a new finding/update to a reported event shall be reported immediately, but not later than 7 calendar days following the date of awareness by the sponsor of the new reportable event or of new information in relation with an already reported event.

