#### Criteria for discontinuing or modifying allocated interventions {11b}

Once the patient is allocated to the control or interventional arm the patient can still be excluded from the study in case the intraoperative eligibility criteria are not met or in case the first PEEP test was not considered safe for the patient. Once the allocated intervention has been applied, this can be modified in case the patient reaches the primary outcome during the surgery (intraoperative CSF leakage at the third PEEP test). In such case, the neurosurgeon can undertake any actions deemed necessary to ensure optimal patient care in the situation.

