##### Intraoperative data

The device used and its size, LOT number, size of trepanation, any use of autologous material, and type of suture are recorded.

To determine the intraoperative CSF leak before and after the application of the device, the PEEP will be increased to 20 cmH2O for 20 s. First, this test will be performed before closure of the dura to determine safety for the postoperative intracranial field (control of hemorrhage, swelling or other potential adverse effects). Upon completion of the primary sutured dural closure and before the application of the sealant, the closure of the dura will be evaluated for CSF leakage by repeating the test. The patient is excluded if there is no leakage at PEEP of 20 cmH2O for 20 s. Two minutes after application of the device, the test will be performed for a third time to evaluate CSF leakage. All 3 PEEP elevations and application of the device will be recorded on video. A photograph will be taken before and after device application.

After the procedure, end users (surgeons, scrub nurses) will be invited to complete several closed-end questions regarding their user experience with LIQOSEAL.

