#### Data management {19}

An electronic data capturing (EDC) system will be used to collect data on a secure, Internet-based electronic case report form (e-CRF), and image transfer software. The principal investigator (PI) or his/her designee at the clinical site will perform primary data collection by entering the data into the e-CRF. Only the PI or other predesignated personnel will be authorized to enter data using their unique login credentials. Each user access to the system will be tracked so that all data operations can be monitored and verified.

The e-CRF will be completed on a continuous basis starting from the point of enrollment to final follow-up.

A critical quality control shall be performed for the first 2 subjects by the sponsor’s designated data management team and queries issued where needed. Such queries must be reviewed by the monitor prior to alerting the site personnel to answer them.

After the monitor has done the source document verification and obtained satisfactory answers to eventual queries from the site, a full quality control shall be performed on the monitored data throughout the clinical investigation by the designated data management team and queries issued where needed. This process will be repeated till the end of the clinical investigation so as to allow for a timeline freezing of the data base for statistical analysis.

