### Statistical methods

#### Statistical methods for primary and secondary outcomes {20a}

The primary analysis set will consist of a modified intention to treat analysis (mITT). Modified intent-to-treat (mITT) analysis set is a subset of ITT analysis set and will consist of all enrolled subjects (subjects who have signed the ICF, meet all inclusion criteria, meet none of the exclusion criteria and the investigational/control device has contacted the subject’s dura) with evaluable data for the primary endpoint.

The primary endpoint will be evaluated for statistical significance based on the Wald method for difference of proportions. If non-inferiority is met a one-sided significance level of 5%, the difference in success rates will also be evaluated for superiority at a one-sided significance level of 5%.

The primary endpoint will also be summarized by investigational site and cranial procedure type. Interactions of treatment and site/procedure type may be examined graphically or using logistic regression with success rate at day 90 as the response variable, and the study center (or procedure type), treatment group, and study center (or procedure type) by treatment group interaction as predictor variables in the model. If the results of the test show evidence of heterogeneity across sites/procedure types (i.e., *p*-value<0.15), then the treatment/procedure type effect will be evaluated further to identify any confounding factors.

All safety analyses will be based on subjects in the intention-to-treat (ITT) analysis set. The ITT analysis set will consist of all enrolled subjects (subjects who have signed the ICF, meet all inclusion criteria, meet none of the exclusion criteria, the investigational/control device has contacted the subject’s dura). Results based on the ITT analysis set will be analyzed according to each subject’s randomization assignment.

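### As written, adverse event reporting starts at an enrolment that is defined only by device contact, so harms from the two earlier PEEP tests can fall outside the safety record

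*Protocol article*

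**What the plan says.** **Reporting window.** Adverse event reporting and harms {22} opens with "During the study, (serious) adverse events and (serious) anticipated and unexpected adverse device effects will be recorded" and then sets the window: "reporting will be done from point of enrolment till end of study". Data management {19} ties the data form to the same event: "The e-CRF will be completed on a continuous basis starting from the point of enrollment to final follow-up".

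**Who is enrolled.** The only definition is in Statistical methods for primary and secondary outcomes {20a}, given once for the mITT set and once for the ITT set. Beyond consent and the inclusion criteria, a subject must "meet none of the exclusion criteria and the investigational/control device has contacted the subject’s dura". The same section adds: "All safety analyses will be based on subjects in the intention-to-treat (ITT) analysis set".

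**Order of events in theatre.** Sequence generation {16a} places randomisation at the start of surgery. Intervention description {11a} then lists the first PEEP test, suturing of the dura, the second PEEP test, application of the device, and the third PEEP test.

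**What the early tests are for.** Intraoperative data, under {18a}, says the first test is done "to determine safety for the postoperative intracranial field (control of hemorrhage, swelling or other potential adverse effects". The second checks the sutured closure, and a patient without a leak is excluded. Criteria for discontinuing or modifying allocated interventions {11b} lets an already allocated patient be excluded when intraoperative criteria are not met, or "in case the first PEEP test was not considered safe for the patient".

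**The concern.** Raising PEEP to 20 cmH2O for 20 s before any device is used is a study procedure, and the article itself names possible harms of the first test. If enrolment means what the statistical section says, the sequence works against safety ascertainment. A patient who bleeds or swells at the first test is excluded because of that harm, does not become enrolled, and so has no reporting period. A patient excluded after the second test for want of a leak has been exposed twice and is in the same position. Even in a patient who goes on to receive a device, a harm at test 1 or 2 predates the stated start of reporting.

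Safety is part of the stated objective. The DMC judges safety from adverse events ({5d}, {21a}), and the FDA is to receive 90-day safety data on the first 30 patients before enrolment is completed ({21b}). Both depend on what is recorded and for whom.

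**Working it through.** The point is textual, so the check sets the sections side by side.

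1. **Start of the window.** {22} and {19} both say enrolment. Neither defines it.
2. **Meaning of enrolled.** {20a} requires consent, all criteria met and device contact with the dura. The Abstract agrees with this usage: 228 are to be enrolled, and 114 + 114 = 228 are to receive a device.
3. **Position of the tests.** By {11a}, PEEP tests 1 and 2 both precede device contact. Only test 3 follows it.
4. **Combining 1 to 3.** If the {20a} definition carries over to {22}, tests 1 and 2 lie before the window for every patient. Those excluded at or after these tests never enter it.
5. **Sections pointing the other way.** {16a} randomises at the start of surgery within the platform that also captures the data. {18a} collects preoperative and pre-device intraoperative data, which need a form before device contact. {11b} speaks of excluding an allocated patient from the study, so that patient was already in it. The carry-over in step 4 is therefore an inference.
6. **The part that needs no inference.** {20a} bases all safety analyses on the ITT set and defines that set by device contact. A patient excluded before the device is in no safety analysis, whatever enrolment means in {22}.

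**Size.** The planned total reproduces. With 91% success in both arms, a 10-point margin, one-sided 5% and 80% power, n per arm = 2 × 0.91 × 0.09 × (1.645 + 0.842)² / 0.10² ≈ 101.3, rounded up to 102. Then 102/0.90 = 113.3, rounded up to 114, which gives 228. This says nothing about how many patients are excluded in theatre, and the article gives no such rate.

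Purely as an assumption, suppose a share f of PEEP-tested patients is excluded before device contact and 228 are treated. The number tested but not treated is 228f/(1 − f):

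| f (assumed) | tested, not treated |
|---|---|
| 10% | 25 |
| 20% | 57 |
| 30% | 98 |
| 50% | 228 |

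These are patients exposed, not events.

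**The case against.** The strongest reply is that a membership rule for analysis sets has been borrowed to date the start of data collection. The harms section does not define enrolment, and its opening clause covers events during the study without a start point. The sections in step 5 of the working fit an earlier enrolment better. The retention section {18b} also preserves data from withdrawn subjects. This is a condensed article: the SPIRIT schedule and study scheme are figures not shown, and the full protocol may define enrolment operationally.

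Much of this stands. A reader might infer that harms of the PEEP tests are never captured, that every event in an excluded patient goes unreported, or that the DMC and FDA would see only patients who tolerated the tests. The documents do not support any of these as fact, because the start of enrolment in practice is not shown.

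The reply does not remove the point. No section states another start, such as consent or randomisation. The retention section concerns withdrawal, does not mention exclusion during surgery, and keeps only data already collected for whichever analyses apply. This is also more than detail left to a fuller document: the article states a start point and a definition that conflict with its own data collection, and it states a safety set that leaves these patients out.

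**Conclusion.** The point holds in a limited form. The article uses enrolment inconsistently. On the only definition given, harms from PEEP tests 1 and 2 fall before the reporting window. Independently of that reading, patients excluded before device contact are outside every safety analysis. The first conclusion rests on applying the {20a} definition to {22} and {19}; the second rests on {20a} alone.

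Three stronger readings should be resisted:

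- **A count of patients lost.** The range of 25 to 98 for assumed exclusion rates of 10% to 30% is illustration only. Some intraoperative exclusions in {10}, such as wound class, gap size or coverage, are not PEEP results and need not follow a test. The number affected is unknown.
- **Bias in the device comparison.** Tests 1 and 2 come before the surgeon is unblinded and are the same in both arms, so the gap does not directly distort that comparison. It concerns the safety record and oversight.
- **Both tests as enrichment.** Test 1 is a safety check. Only test 2 selects leaking closures.

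The change should be made, because a literal application of the rules drops harms of a study procedure when those harms cause exclusion.

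**What to change.** Reconcile {19}, {20a} and {22} so that enrolment has one meaning, or so that the reporting start no longer depends on the word:

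- In {22} and {19}, start adverse event reporting and the e-CRF at randomisation, or at the latest at the first PEEP elevation, for every consented patient.
- Record events in patients excluded during surgery on a short e-CRF form, with the reason for exclusion, and state until when events are collected for them.
- In {20a}, keep the device-contact set for the comparative analysis, and add a separate listing of events in patients excluded during surgery and of events arising at PEEP tests 1 and 2. Supply it to the DMC and include it in the FDA safety package.

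The cost is a short extra form and a listing. Any collection of events in excluded patients beyond the operation adds some site work, depending on the period chosen. No study procedure, clinical rule or sample size changes.
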